## Abstract

**Background:**

Smoking rates, and associated negative health outcomes, are disproportionately high among people with mental illness compared to the general population. Smoke-free policies within mental health hospitals can positively impact on patients’ motivation and self-efficacy to address their smoking. However, without post-discharge support, preadmission smoking behaviours typically resume. This protocol describes a randomised controlled trial that aims to assess the efficacy of linking mental health inpatients to community-based smoking cessation supports upon discharge as a means of reducing smoking prevalence.

**Methods/Design:**

Eight hundred participants with acute mental illness will be recruited into the randomised controlled trial whilst inpatients at one of four psychiatric inpatient facilities in the state of New South Wales, Australia. After completing a baseline interview, participants will be randomly allocated to receive either: ‘Supported Care’, a multimodal smoking cessation intervention; or ‘Normal Care’, consisting of existing hospital care only. The ‘Supported Care’ intervention will consist of a brief motivational interview and a package of self-help material for abstaining from smoking whilst in hospital, and, following discharge, 16 weeks of motivational telephone-based counselling, 12 weeks of free nicotine replacement therapy, and a referral to the Quitline. Data will be collected at 1, 6 and 12 months post-discharge via computer-assisted telephone interview. The primary outcomes are abstinence from smoking (7-day point prevalence and prolonged cessation), and secondary outcomes comprise daily cigarette consumption, nicotine dependence, quit attempts, and readiness to change smoking behaviour.

**Discussion:**

If shown to be effective, the study will provide evidence in support of systemic changes in the provision of smoking cessation care to patients following discharge from psychiatric inpatient facilities.

**Trial registration:**

Australian New Zealand Clinical Trials Registry ANZTCN:
ACTRN12612001042831. Date registered: 28 September 2012.

## Background

Tobacco use is the second leading cause of modifiable morbidity and mortality worldwide
[1]. In Australia, the prevalence of smoking in the general population has halved over the past three decades to approximately 15%
[2]. However, depending on diagnosis and setting, between 33% and 90% of people with mental illness continue to smoke
[3,4]. Patients with psychotic disorders have among the highest smoking prevalence (74% to 88%)
[5]. Smokers with a mental illness also smoke more heavily, are more nicotine dependent and find it more difficult to quit compared to the general population
[5-7]. As a consequence, smokers with a mental illness are more likely to have a chronic disease and to have a shorter life expectancy
[8-11].

For smokers in the general population
[12,13] and for those with a mental illness
[14,15] multimodal smoking cessation interventions, utilising both pharmacological interventions (such as nicotine replacement therapy (NRT)) and psychosocial supports (such as behavioural counselling and self-help materials), have demonstrated efficacy in increasing the likelihood of quitting successfully. Interventions of a longer duration and greater intensity are more efficacious for both groups of smokers
[11,16-18]. Further, neither making a quit attempt nor successfully ceasing smoking has been found to negatively impact on
[14], and may even improve
[19-22], psychiatric health.

Hospitals have been recognised as a key setting for initiating the delivery of smoking cessation care
[17,20,23,24]. The implementation of total smoking bans in mental health hospitals
[11,25] and the ensuing need to manage inpatient nicotine withdrawal
[12,26] reinforces the need to provide smoking cessation treatment in this setting
[27]. Evidence suggests that the initiation of smoking cessation treatment in the inpatient psychiatric setting also increases patient motivation and self-efficacy to change their smoking behaviour, both as an inpatient and following discharge
[28]. However, as is the case in general medical settings
[29], evidence from psychiatric settings suggests that without post-discharge support smoking is likely to return to preadmission levels within 2 weeks
[30]. Such findings suggest a need for adequate and consistent support to encourage a sustained quit attempt and prevent relapse
[30-32]. Systematic review evidence from general medical settings suggests that multimodal post-discharge cessation support of at least 4 weeks in length or greater can result in higher rates of successful smoking cessation
[17].

A recent randomised controlled trial has demonstrated the effectiveness of linking mental health inpatients to community-based smoking support following discharge. Prochaska and colleagues
[20] reported a significant difference in point prevalence abstinence at 18 months post-discharge; 20% and 7.7% for intervention and control conditions, respectively. Over a period of up to 6 months post-discharge, intervention group participants were able to take up both pharmacological (NRT for a total duration of up to 10 weeks) and psychosocial (face-to-face, computer-based, and self-directed reading) smoking cessation support, tailored to their readiness to stop smoking. An opportunity may exist to enhance and extend such positive findings by providing multi-modal smoking cessation support to all smokers, proactively and intensively, immediately following discharge, regardless of assessed readiness to change.

To assess the feasibility of such an approach we conducted a pilot randomised controlled trial of an intervention consisting of the provision of psychological and pharmacological support to smokers admitted to one inpatient psychiatric facility. Inpatient smokers were randomly allocated to a multimodal smoking cessation intervention or treatment-as-usual control. Smoking cessation treatment was initiated for all smokers during admission and continued for a 4-month period post-discharge with assessments made at 1 week and at 2, 4 and 6 months
[33]. At the end of treatment (4 months), participants in the intervention group had significantly higher rates of 7-day point prevalence abstinence than controls (11.5% versus 2%), but this difference was not sustained at 6 months follow-up
[34]. Based on the findings of these previous studies, the objective of this study is to conduct a randomised controlled trial to test the effectiveness of a multi-modal smoking cessation intervention, initiated within mental health inpatient facilities for all smokers and continued post-discharge, on 12-month post-discharge smoking cessation rates.

## Methods/Design

### Study design and setting

A randomised controlled trial with blinded follow-up will be conducted (Figure 
1). Participants will be recruited as inpatients at one of four acute mental health facilities within one Local Health District in New South Wales, Australia. At the time of recruitment, participants will be randomly allocated to either an intervention (Supported Care) or control (Normal Care) group. Participants allocated to the Supported Care condition will receive a brief motivational interview and a package of self-help material for abstaining from smoking whilst in hospital, and intensive psychosocial and pharmacological support for 16 weeks upon hospital discharge. Participants in the Normal Care condition will receive standard hospital and discharge smoking cessation care.

**Figure 1 F1:**
[figure not shown]
**Study design.** ASAP, as soon as possible; CATI, computer-assisted telephone interview; NRT, nicotine replacement therapy.

Follow-up assessments will be conducted at 1, 6 and 12 months post-discharge for both conditions. The primary outcome measures comprise 7-day point prevalence of smoking abstinence and prolonged smoking abstinence. Secondary outcome measures will include number of cigarettes smoked per day, nicotine dependence, quit attempts, and readiness to change smoking behaviour. The effect of the intervention will be assessed by comparing primary and secondary outcome measures between intervention and control groups at each follow-up point.

Ethics approval for the study has been obtained from the Hunter New England Human Research Ethics Committee, HNEHREC reference no.: 11/12/14/4.02, and the University of Newcastle Human Research Ethics Committee, reference no.: H-2012-0061. The trial is registered on the Australian New Zealand Clinical Trials Registry ACTRN12612001042831. Date registered: 28 September 2012.

### Recruitment process and inclusion criteria

Research staff (independent of the hospitals), all of whom will receive standardised training in mental illness and its impacts, will approach nurse unit managers in the four units on a daily basis to identify newly admitted patients. The nurse unit managers will advise whether individual patients are sufficiently psychiatrically stabilised and capable of completing the baseline interview. If so, patients will be approached to determine if they meet the eligibility criteria to participate in the study. Patients will be eligible if they: are a current smoker (smoked cigarettes daily, weekly or less than weekly in the month prior to admission); 18 years of age or above; understand the research, have capacity to ask and answer questions in relation to the benefits and potential harms (that is, have capacity to give informed consent); and are willing to provide contact details (including phone number and mailing address) to facilitate communication once discharged. No exclusion criteria will be applied. Patients who meet the eligibility criteria will be given a detailed explanation of the project requirements and invited to participate in the trial. Informed consent will be gained from all participants. Patients who elect not to take part, and who are subsequently readmitted to the facility during the recruitment phase, will be re-approached and re-offered the opportunity to participate. Patients will only be recruited once, regardless of the number of readmissions within the study recruitment phase. Eight hundred participants will be recruited over a period of 18 months.

### Randomisation, allocation concealment and sequence generation

A random allocation sequence using permuted block randomisation (with a block size of ten) will be generated by a statistician independent of the project prior to the commencement of recruitment. Randomisation will be carried out separately by site and stratified by diagnosis type to account for differences in smoking levels and nicotine dependence (psychosis/non-psychosis type diagnosis)
[5,35]. Participant allocation to group (1:1 ratio) will occur immediately post-baseline data collection. Research staff will provide participants with a sequentially numbered, opaque, sealed envelope. The envelope will contain a coloured piece of paper that indicates allocation to either the Supported Care or Normal Care condition. Research staff involved in recruitment and outcome data collection will be blind to the order of patient condition assignment.

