#### Supported care

In addition to standard smoking care provided by the hospital, participants allocated to the Supported Care condition will be provided with a range of evidence-based smoking cessation supports
[12,18]. Following the baseline interview, supported care participants will be provided with smoking cessation written self-help material
[39], including information tailored to people with mental illness
[40-42] and NRT usage advice, and a brief motivational interview (10 to 15 minutes) designed to evoke ambivalence regarding smoking behaviour and reinforce positive intentions to address smoking
[43]. Content of the motivational interview will encourage consideration of: lifestyle behaviours; pros and cons of both continuing to smoke and quitting; impact of smoking on life in 5 years from the time of interview; and importance of and confidence to quit
[43].

Upon discharge from hospital, all Supported Care participants will receive a standard project pack of NRT, which contains: seven nicotine patches (21 mg); one nicotine inhaler with six cartridges (10 mg); 30 pieces of nicotine gum (4 mg); and 20 nicotine lozenges (4 mg). NRT discharge packs will also contain a brief tip sheet for NRT use and the management of NRT side effects, as well as a project reminder card outlining each aspect of the intervention. Within participating units, the process for providing discharge NRT packs will be negotiated in consultation with nurse unit managers and treating staff, in accordance with usual protocols for discharge, and storage of medications. The participant’s general practitioner and, if applicable, community mental health team will be notified of their clients’ involvement in the project, via the standard and automated delivery of discharge records to relevant health professionals, and asked to support their participation in the project
[17].

Once discharged from hospital, participants in the Supported Care arm will receive up to 16 weeks of psychosocial
[44] and 12 weeks of pharmacological support
[12,13,45]. Psychosocial support will initially be delivered through five weekly telephone support calls, followed by 7 weeks of weekly or fortnightly telephone support calls (tailored based on participants preference), tapering to 4 weeks of fortnightly support calls between weeks 12 and 16 (Figure 
1). The content of the calls will be delivered utilising a framework of motivational interviewing techniques

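### A single fixed block size of ten per site-by-diagnosis list leaves up to 17% of allocations deducible, so sealed envelopes alone do not secure recruiters' blindness to order

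*Protocol article*

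**What the plan says.** The section on randomisation, allocation concealment and sequence generation in the protocol article states:

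- **Method:** "A random allocation sequence using permuted block randomisation (with a block size of ten"). An independent statistician prepares the sequence before recruitment starts.
- **Lists:** "Randomisation will be carried out separately by site and stratified by diagnosis type" (psychosis or non-psychosis).
- **Timing and ratio:** "Participant allocation to group (1:1 ratio) will occur immediately post-baseline data collection".
- **Device:** "Research staff will provide participants with a sequentially numbered, opaque, sealed envelope". On its content: "The envelope will contain a coloured piece of paper that indicates allocation to either the Supported Care or Normal Care condition".
- **Blinding:** "Research staff involved in recruitment and outcome data collection will be blind to the order of patient condition assignment".

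The Study design and setting section gives the number of sites: "Participants will be recruited as inpatients at one of four acute mental health facilities". The Supported care section describes what follows allocation on the ward: "Following the baseline interview, supported care participants will be provided with smoking cessation written self-help material", together with a motivational interview of 10 to 15 minutes. The Process measures section confirms that this interview comes after assignment and is for Supported Care only.

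**The concern.** An opaque envelope hides the next slip. It does not stop anyone from deducing that slip from earlier ones when every block has the same known length. Once five of ten in a block have gone to one arm, the rest of the block is determined.

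Past allocations could become known here because the treatment is open on the ward: one arm gets material and an interview during the admission, the other does not. The article also words its blinding claims differently. Under Primary outcome measures, the staff who take breath samples are said to be blind to the participant's group. Recruiters are said only to be blind to the order of assignment, which leaves open whether they learn past allocations.

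Assignment follows consent and baseline interview, so an allocation cannot easily be altered. What remains possible is selective or timed enrolment, with a more motivated patient meeting a slot that someone expects to be Supported Care. The Sample size section plans for 1% versus 5% prolonged abstinence. At 400 per arm that is 0.01 × 400 = 4 versus 0.05 × 400 = 20 abstainers, so a few selectively enrolled patients could matter.

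**Working it through.** The article gives no figure for predictability, so there is none to reproduce. The sample size does not enter the calculation.

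**Inputs from the article**
- Block size 10 at 1:1, so h = 5 per arm per block.
- 4 sites × 2 diagnosis types = 8 lists.
- 800 participants planned, so 800 / 8 = 100 per list on average, or 10 blocks.

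**Assumed observer:** knows the block size, all earlier allocations in the list, and the list from which the next patient will draw.

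**Certain allocations.** These are the slots left once one arm is used up. The expected number of one arm's slots that fall after the last slot of the other arm is h/(h + 1). Counting both arms:

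2h/(h + 1) = 10/6 = 1.67 per block, or 16.7%.

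Over the trial: 0.1667 × 800 ≈ 133. The tenth slot is always certain.

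**Best guess.** The observer always names the arm with more slots left in the block. Expected correct guesses:

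h + ½ × [4^h / C(2h, h) − 1] = 5 + ½ × (1024/252 − 1) = 6.53 of 10, or 65.3%, against 50% by chance.

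An exact recursion over block composition gives the same values and allows comparison with other designs. The rows for varying sizes come from simulating lists of 100 with the sizes equally likely; the observer knows the set of sizes but not which is in force. The sizes are illustrative.

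| Design | Certain | Best guess correct |
|---|---|---|
| Fixed 4 | 33.3% | 70.8% |
| Fixed 6 | 25.0% | 68.3% |
| Fixed 10 (plan) | 16.7% | 65.3% |
| Random 6/8/10 | about 1.5% | about 66% |
| Random 8/10/12 | about 1.2% | about 65% |

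At 800 participants, 1.5% is 12 certain allocations and 1.2% is about 10, against 133. Varying the size removes nearly all the certainty and almost none of the guessing advantage.

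**Why 133 is an upper bound.** It requires complete blocks, perfect tracking of every list, and knowledge of the stratum before the patient is approached. Certain slots lie at the end of a block, so a part-used last block lowers the count.

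**The case against.** The strongest reply is that the article does not show that such an observer exists.

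- It does not say who opens the envelope, whether recruiters see the slip, or who delivers the motivational interview. A condensed article may leave these to the full protocol.
- A block size printed in an article is not shown to have been known to recruiters during enrolment.
- Under Data collection procedures and Patient characteristics, diagnosis is taken from medical records after the baseline interview. When a patient is approached, the procedure does not give the recruiter the stratum, so two lists per site are in play.
- Under Recruitment process and inclusion criteria, nurse unit managers advise on stability and capability only. Patients judged suitable are then approached under stated eligibility criteria.
- The design has real safeguards: an independent statistician, a sequence made in advance, numbered opaque sealed envelopes, and allocation after baseline. Ten is less predictable than fixed blocks of four or six.
- Varying the block size does not lower best-guess accuracy.

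All of this stands. A reader might infer that recruiters see every allocation and can predict later ones, or that the blinding statement is false; the article supports neither. What the reply does not remove is that a constant block size is a choice the plan states. The safety of that choice depends on staff not learning past allocations, the block size and the stratum, and the envelopes do not ensure that.

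**Conclusion.** The point holds in conditional form and is of minor weight. If staff who enrol learn past allocations, the block size and the patient's stratum, up to 1.67 of 10 allocations (at most about 133 of 800) are certain and a best guess is right 65% of the time. In that case opaque envelopes alone do not secure the stated blindness to order. The 133 should not be read as an estimate of allocations actually predicted, and nothing in the article shows that selection took place. Sample size and power are unaffected.

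**What to change.** 1. **Unused envelopes.** Have the independent statistician issue new lists with randomly varying block sizes within site and diagnosis, and withhold the sizes from recruiting and ward staff. Sizes such as 6/8/10 or 8/10/12 bring certain allocations to about 1-2%. The guessing advantage stays near 65%, so the gain should be described as removing certainty.
2. **Blinding statement.** Keep it for outcome-data staff. For recruiters, limit it to what the procedure secures, and state who opens the envelope, whether recruiters learn past allocations, and whether the block size is withheld from them.
3. **Participants already enrolled.** For each slot, compute the probability of Supported Care given the earlier allocations in its block (Supported Care slots left divided by all slots left). Check whether baseline characteristics vary with that probability. Use measures the article lists at baseline in both arms, such as age, education, employment, smoker identity, alcohol use, psychological distress and perceived stress. Nicotine dependence and readiness are listed only as follow-up outcomes, and the importance and confidence ratings exist for Supported Care only, so the article does not show that these could serve.

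**Cost:** new lists and envelopes, and a slightly larger possible imbalance within lists (half a block: 6 with a block of twelve against 5 now, plus any block abandoned part-way). Trial status gives recruitment from October 2012 to a planned end in April 2014, so step 1 helps only for what remains. Steps 2 and 3 remain useful after recruitment ends.

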### Data collection procedures

For eligible and consenting patients, baseline data will be collected during admission via a face-to-face baseline interview, administered by research staff in a quiet area of the unit. The baseline data collection interview will be developed based on previous pilot research undertaken by the research team
[33]. After the completion of the baseline interview, clinical and demographic information will be collected by research staff from patient medical records.

Follow-up data will be collected via computer-assisted telephone interviews (CATI) from all participants at 1, 6 and 12 months post-discharge. In addition, process data will be collected during support calls to assess intervention uptake.

### Intervention

#### Normal care

Participants allocated to the Normal Care condition will receive standard hospital smoking care only, as routinely delivered by hospital staff. This may include brief advice to quit, provision of NRT whilst admitted to the inpatient facility, up to 3 days supply of NRT upon discharge, and/or a referral to Quitline as per mandatory local area health guidelines
[26,36]. Previous research suggests that standard hospital care is likely to be limited
[37,38].

#### Supported care

In addition to standard smoking care provided by the hospital, participants allocated to the Supported Care condition will be provided with a range of evidence-based smoking cessation supports
[12,18]. Following the baseline interview, supported care participants will be provided with smoking cessation written self-help material
[39], including information tailored to people with mental illness
[40-42] and NRT usage advice, and a brief motivational interview (10 to 15 minutes) designed to evoke ambivalence regarding smoking behaviour and reinforce positive intentions to address smoking
[43]. Content of the motivational interview will encourage consideration of: lifestyle behaviours; pros and cons of both continuing to smoke and quitting; impact of smoking on life in 5 years from the time of interview; and importance of and confidence to quit
[43].

Upon discharge from hospital, all Supported Care participants will receive a standard project pack of NRT, which contains: seven nicotine patches (21 mg); one nicotine inhaler with six cartridges (10 mg); 30 pieces of nicotine gum (4 mg); and 20 nicotine lozenges (4 mg). NRT discharge packs will also contain a brief tip sheet for NRT use and the management of NRT side effects, as well as a project reminder card outlining each aspect of the intervention. Within participating units, the process for providing discharge NRT packs will be negotiated in consultation with nurse unit managers and treating staff, in accordance with usual protocols for discharge, and storage of medications. The participant’s general practitioner and, if applicable, community mental health team will be notified of their clients’ involvement in the project, via the standard and automated delivery of discharge records to relevant health professionals, and asked to support their participation in the project
[17].

Once discharged from hospital, participants in the Supported Care arm will receive up to 16 weeks of psychosocial
[44] and 12 weeks of pharmacological support
[12,13,45]. Psychosocial support will initially be delivered through five weekly telephone support calls, followed by 7 weeks of weekly or fortnightly telephone support calls (tailored based on participants preference), tapering to 4 weeks of fortnightly support calls between weeks 12 and 16 (Figure 
1). The content of the calls will be delivered utilising a framework of motivational interviewing techniques
[46], and incorporate behavioural strategies to assist with addressing smoking. Support call staff will prompt participants to utilise the Quitline, and offer to send a Quitline referral on their behalf. Support calls will be delivered by research staff that either have a relevant allied health qualification and/or experience working with people with mental illness. All support callers will receive both standardised mental health training and ongoing motivational interviewing based training and supervision from an experienced clinical consultant.

Ongoing NRT provision will be offered by research staff to all supported care participants, with delivery by mail. The amount and frequency of NRT provided will vary by participant in accordance with personal preference, degree of nicotine dependence (measured using time to first cigarette)
[47], and nicotine withdrawal symptoms
[48]. Within the initial 12 weeks of support post-discharge, participants are able to optionally elect any combination of the following NRT products: patches (21, 15, 14 or 7 mg); lozenges and/or mini lozenges (2 and 4 mg); gum (a variety of flavours; 2 and 4 mg); inhalers (10 and 15 mg refill cartridges); oral spray (one dispenser contains 150 × 1 mg sprays); and oral strips (2.5 mg). Pharmacological support will be provided in accordance with an evidence-based, combination NRT algorithm aimed at smokers with a high level of nicotine dependence and who have more difficulty quitting
[49].

